## Methods

### Design

ENFORCE focal is a pragmatic multicentre, RCT comparing the (cost-)effectiveness of focal therapy to radical whole-gland treatment, that is, RP or RT, in patients with intermediate-risk PCa. Patient recruitment will be performed in outbound patient clinics in six Dutch centres and their networks. Each participating centre performs a focal ablation technique and radial whole-gland treatment. Focal therapies applied in the study are TULSA, HIFU and IRE; each centre performs one of the focal therapies. Radical treatment will be performed as per normal routing. This means that RP will be performed by the urologist in the participating centres or in their collaborative network, and patients choosing RT will be referred to RT centres. Within the trial, one of the participating centres collaborates with a dedicated HIFU clinic where the focal treatment is carried out. Follow-up will be at least 3 years, with a maximum of 5 years to gain information regarding long-term outcomes. The set follow-up visits are 6 weeks, 3 months, 6 months, 12 months and yearly thereafter. At the follow-up visits clinical data will be collected, and questionnaires regarding QoL and costs will be administered. Furthermore, at 9 months and 18 months PSA will be monitored in both groups in alignment with European guidelines on follow-up after RP and RT. For the focal therapy arm, at 12 months, an MRI and prostate biopsies will be performed. In the years thereafter, a prostate MRI will be performed yearly with additional biopsies on indication, such as rising PSA levels over time, suspicious MR findings in the treated zone or newly identified lesions outside the treated area.

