#### Secondary endpoints

Secondary endpoints include metastasis-free survival, generic and disease-specific patient-reported health-related QoL using validated questionnaires, oncologic safety, disease progression, disease-specific mortality, all-cause mortality, adverse events, operating time, hospital care stay, pathology results, resources use and productivity loss using validated questionnaires and cost-effectiveness. The questionnaires will be completed online using a secure web-based module at baseline and at specific follow-up intervals, that is, 6 weeks, 3 months, 6 months, 12 months and annually thereafter for up to 60 months.

For the patient-reported health-related QoL outcomes, patients will use a set of six validated questionnaires. QoL is measured at baseline and at set points during follow-up.

For the other secondary endpoints the following questionnaires will be used: European Organisation for Research and Treatment of Cancer QoL questionnaire prostate 25 (EORTC QLQ PR-25), international consultation on incontinence questionnaire (ICIQ), international prostate symptom score (IPSS), sexual health inventory measurement international index of erectile dysfunction (SHIM IIEFF-5), EuroQoL 5 dimensions five-level version (EQ-5D-5L). The EORTC QLQ PR-25 is a questionnaire to assess sexual problems and functioning, micturition, bowel symptoms and hormonal treatment side effects. This questionnaire contains 25 questions regarding those aspects. The ICIQ is used to assess urinary function and its impact on QoL and contains four questions. IPSS is a questionnaire for assessment of the degree of lower urinary tract symptoms and QoL. This score consists of seven questions and an overall score on quality of miction. The SHIM IIEF-5 used is the 5-item version of the IIEF. This questionnaire assesses erectile function and contains five questions. The EQ-5D-5L is a questionnaire that assesses general health in five dimensions. These dimensions are mobility, self-care, usual activities, pain/discomfort and anxiety/depression. Further, a visual analogue scale (VAS) is used to provide a quantitative measure of the perception of overall health of a participant.

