Two questionnaires will additionally be used regarding cost-effectiveness analyses. The iMTA productivity cost questionnaire (iPCQ) is used to assess productivity loss in terms of absence from work due to illness. The iMTA medical costs questionnaire (iMCQ) is used to determine healthcare consumption, including hospital visits and domestic help.

In the secondary endpoints, clinical outcomes are included, such as operating time and hospital care stay. Operating time will be registered for focal therapies as the time between the start of imaging and the last performed imaging and for RP as the time from the start of incision until closing. For RT, we will register the type of radiation given. Further, data will be collected on treatment-related complications occurring during or after the procedure. During follow-up oncologic safety, in terms of disease progression, metastasis-free survival, disease-specific mortality and all-cause mortality, will be assessed using PSA, MRI and biopsies, as well as data from a national registry. Pathology results from surgery and biopsies will be collected. In addition to the questionnaires for cost-effectiveness analysis, hospital resource use will be recorded.

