### Patient characteristics

Patients aged 40 years and older with localised unilateral dominant PCa, a PSA≤20 ng/mL and normally eligible for general anaesthesia will be included in this study. All inclusion and exclusion criteria are listed in table 1. Patients will be included after being diagnosed with intermediate-risk PCa and having completed the diagnostic work-up according to national guidelines. At a minimum, all patients will have undergone clinical examination, PSA testing, prostate MRI and prostate biopsies. Additional staging procedures are not part of standard staging for this risk category in the Netherlands.

**Table 1 T1:** Inclusion and exclusion criteria. To be able to participate in this study, patients must meet all inclusion criteria and cannot meet any of the exclusion criteria

Inclusion criteria	Exclusion criteria
Men, age of 40 years or over, with unilateral clinically significant intermediate-risk PCa or dominant unilateral clinically significant intermediate-risk and small contralateral low-risk (ISUP) one disease	Unfit for general anaesthesia or radical surgery
Gleason score of 7 (3+4 or 4+3; ISUP grade 2/3)	Low-volume low-risk disease (≤4 mm Gleason score of≤6/ISUP grade 1)
PSA level of≤20 ng/mL	High-risk disease (Gleason score of≥8/ISUP grade>3)
Clinical stage≤T2b disease	Clinical cT2c or T3 disease (extracapsular PCa)
Life expectancy of≥10 years	Men who have received previous active therapy for PCa
Men with a prostate size≤5 cm in sagittal length or≤6 cm in axial length	Men with evidence of extraprostatic disease
Fit, eligible and normally destined for radical surgery or radiotherapy	Men with an inability to tolerate transrectal ultrasound
No concomitant cancer	Cardiac pacemaker
No previous treatment of their prostate	Metal implants/stent in the urethra or prostate
An understanding of the Dutch language sufficient to receive written and verbal information about the trial, its consent and the study questionnaires	ASA≥4
	Prostatic calcifications/cysts that interfere with effective delivery of TULSA/HIFU based on MR
	Men with renal impairment and a glomerular filtration rate (GFR) of<30 mL/minute/1.73m2
	Unable to give consent to participate in the trial, as judged by the attending clinicians

GFR, glomerular filtration rate; HIFU, high-intensity focused ultrasound; PCa, prostate cancer; PSA, prostate-specific antigen; TULSA, transurethral ultrasound ablation.

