### Analysis

Descriptive statistics will be used to summarise the data. For the oncological effectiveness, a one-sided 95% upper confidence bound will be created for the percentage difference in pathologically proven recurrent disease and/or (indication for) re-treatment (salvage treatment). If this bound is less than the non-inferiority margin of 15%, focal therapy will be declared to be non-inferior to usual care, that is, RP/RT. For the QoL, outcome differences between the two groups will be calculated with 95% CIs. All data will be analysed according to the intention-to-treat principle, including all randomised participants in the groups to which they were originally assigned, regardless of protocol deviations or loss to follow-up. In addition, to test robustness of the results, per-protocol and as-treated analysis will be performed regarding oncological effectiveness and QoL.

Furthermore, for secondary QoL outcomes, individual item responses will be used to derive the proportion of men reporting a moderate or big problem (or equivalent).

Metastasis-free survival, disease progression, disease-specific mortality and all-cause mortality will be presented with Kaplan-Meier curves. Procedure time and hospital care stay will be summarised using descriptive statistics. Treatment-related complications will be recorded according to the Clavien-Dindo classification. An overall risk difference for the overall complication rate and a 95% CI, and a risk difference per complication and their corresponding 95% CIs will be calculated. Pathology results will be summarised using descriptive statistics.

Cost-effectiveness will be performed from a societal perspective as per Dutch guidelines for economic evaluation.^18^ Costs will be calculated according to the Dutch guideline for costing research. Average costs will be calculated in both groups and differences will be calculated inclusive of 95% CIs. Effectiveness will be measured in terms of quality-adjusted life years (QALYs). These will be based on the utility scores as measured with the EQ-5D-5L, using the area under the curve method. Incremental cost-effectiveness ratios will be calculated by dividing estimated differences in costs by differences in QALYs. Uncertainty will be addressed by means of non-parametric bootstrapping and, where relevant, one-way sensitivity analyses.

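### Disease-specific mortality, and disease progression if death is not an event there, are better shown as cumulative incidence than Kaplan-Meier curves; the effect is small

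*Protocol article*

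**What the plan says.** The Analysis section of the protocol article names one estimator for four outcomes: "Metastasis-free survival, disease progression, disease-specific mortality and all-cause mortality will be presented with Kaplan-Meier curves". It plans no test or hazard ratio for them and gives no censoring rule.

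All four have secondary status. The Secondary endpoints section reads: "Secondary endpoints include metastasis-free survival, generic and disease-specific patient-reported health-related QoL using validated questionnaires, oncologic safety, disease progression, disease-specific mortality, all-cause mortality". The same section groups them as measures of oncologic safety and says that they "will be assessed using PSA, MRI and biopsies, as well as data from a national registry". It does not define disease progression and does not say how a death without progression is counted.

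On duration, the Design section says: "Follow-up will be at least 3 years, with a maximum of 5 years to gain information regarding long-term outcomes". The article mentions neither competing risks nor cumulative incidence. A detailed statistical analysis plan is to follow before database lock.

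**The concern.** Kaplan-Meier treats a censored man as someone who could still have the event later. That is reasonable for a man whose follow-up simply ends. It is not reasonable for a man who has died of something else, because he can no longer die of prostate cancer. If his death is censored, one minus Kaplan-Meier estimates the risk in a hypothetical population without other causes of death, and it exceeds the proportion of men who actually have the event.

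The four outcomes differ in how far this applies:

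- **All-cause mortality:** every death is an event, so Kaplan-Meier is right.
- **Metastasis-free survival:** death is conventionally an event, and then Kaplan-Meier is right.
- **Disease-specific mortality:** other-cause death is a competing event by definition. No reading of the endpoint avoids this.
- **Disease progression:** it depends on whether death counts as an event, which the article leaves open.

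At stake is the reading of absolute risks. The article says that the trial is to inform decisions on reimbursement and standard care, and readers will take percentages from these curves. On the Kaplan-Meier scale, the cancer-death and other-cause-death curves also do not add up to the all-cause curve. Cumulative incidence curves do.

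**Working it through.** The article states no rate of progression, cancer death or other-cause death, so there is no figure to reproduce. The check sizes the overstatement under assumed rates.

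**Inputs from the article.** There are 356 men randomised 1:1, so 178 per arm. Follow-up is 3 to 5 years. Eligibility limits competing deaths: "Life expectancy of≥10 years" and "No concomitant cancer" are inclusion criteria, and "Unfit for general anaesthesia or radical surgery" is an exclusion criterion.

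**Assumptions.** Cause-specific hazards are constant: a for the event and b for other-cause death. Each is set from a net risk by time T: aT = −ln(1 − event risk) and bT = −ln(1 − other-cause risk). Other-cause mortality is varied over 2%, 5% and 10%. With the net risks fixed at T, the results are the same for T = 3 and T = 5 years.

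**Formulas.**

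- One minus Kaplan-Meier, other-cause deaths censored: 1 − exp(−aT)
- Cumulative incidence: a/(a+b) × [1 − exp(−(a+b)T)]

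**Worked example.** Take 20% progression and 5% other-cause death. Then aT = 0.2231, bT = 0.0513 and the sum is 0.2744. The share a/(a+b) is 0.813, and 1 − exp(−0.2744) = 1 − 0.80 × 0.95 = 0.24. Cumulative incidence is 0.813 × 0.24 = 19.5%, against 20% from one minus Kaplan-Meier.

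**Results.**

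| Outcome, one minus Kaplan-Meier | Other-cause death | Cumulative incidence | Overstatement (points) |
|---|---|---|---|
| Disease-specific mortality, 1% | 2% | 0.99% | 0.01 |
| | 5% | 0.97% | 0.03 |
| | 10% | 0.95% | 0.05 |
| Progression, 20% (deaths censored) | 2% | 19.8% | 0.19 |
| | 5% | 19.5% | 0.49 |
| | 10% | 19.0% | 0.98 |
| Progression, 30% (deaths censored) | 2% | 29.7% | 0.28 |
| | 5% | 29.3% | 0.71 |
| | 10% | 28.6% | 1.44 |

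The relative overstatement is about half the other-cause mortality: roughly 1%, 2.5% and 5%.

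**Against sampling error.** The standard error of a 20% risk in 178 men is √(0.20 × 0.80 / 178) = 3.0 points. Gaps of 0.19 to 0.98 points are therefore 0.06 to 0.33 standard errors, or 0.3 to 1.7 men of 178. For 1% disease-specific mortality, 0.05 points is 0.0005 × 178 = 0.09 of a man.

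**Between arms.** With progression of 20% against 25% and equal other-cause mortality in both arms, the Kaplan-Meier difference of 5.00 points becomes 4.89 points on the cumulative incidence scale at 5% other-cause death, and 4.77 at 10%.

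**Adding up.** With 1% cancer death and 5% other-cause death, the two one-minus-Kaplan-Meier values sum to 6.00%. All-cause mortality is 1 − 0.99 × 0.95 = 5.95%. The two cumulative incidences sum to exactly that.

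**The case against.** The strongest objection is that the point is immaterial where it is certain and uncertain where it is material. For disease-specific mortality the overstatement is at most about 0.05 points on the assumed rates, which nobody would see on a plot. The larger figures, 0.5 to 1.4 points, all come from progression, and there the article does not say that deaths are censored. If death counts as an event, as in progression-free survival, Kaplan-Meier is correct. These are also men fit for radical treatment, with a long life expectancy and short follow-up. Randomisation is stratified by age group, so other-cause mortality should be similar in the two arms. Finally, how death is handled for progression is ordinary detail for the analysis plan still to come.

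Most of this stands. A reader might infer that the article plans to censor deaths in the progression analysis. Listing disease progression separately from metastasis-free survival and all-cause mortality does suggest that death is not an event, but no sentence says so, and that half of the point has to stay conditional. The missing definition is not itself a fault in a condensed article.

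The objection does not remove the point on disease-specific mortality. The article names the estimator outright, so this is a stated choice and not an omitted detail. A better estimator exists that uses data the trial already needs. Smallness sets the priority of the change but does not make Kaplan-Meier the right curve for that outcome.

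**Conclusion.** The point holds as a minor improvement at the lowest severity. The planned Kaplan-Meier curve for disease-specific mortality overstates the actual risk, by at most about 0.05 points if that risk is 1% and other-cause mortality is no more than 10%. For disease progression the overstatement is about 0.5 to 1.4 points at 20% to 30% progression and 5% to 10% other-cause death, and only if death is not a progression event. All rates and the constant hazards are assumptions. The direction does not depend on them, but the size does. The calculated gaps lie well within sampling error.

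A reader might go further and infer that these curves are the trial's evidence on oncological safety, so that the non-inferiority conclusion is biased. The article does not support that. The co-primary oncological comparison is a difference in failure percentages at 36 months, judged by a one-sided 95% upper bound against a 15% margin, and it does not use Kaplan-Meier. The four curves are descriptive, and Kaplan-Meier suits two of them (metastasis-free survival provided that death is an event). No co-primary conclusion changes.

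**What to change.** Settle three things in the analysis plan before it is finalised:

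1. Present disease-specific mortality as an Aalen-Johansen cumulative incidence curve per arm, with other-cause death as the competing event.
2. State whether death is an event for disease progression. If it is not, present progression in the same way, with other-cause death as the competing event. If it is, keep Kaplan-Meier and name the endpoint accordingly.
3. Keep Kaplan-Meier for all-cause mortality and for metastasis-free survival, stating that death is an event in the latter.

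The cost is a sentence or two and standard software. Date and cause of death are already needed for the two mortality endpoints, so no new data are collected. The sample size and the co-primary analyses are unaffected.

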## Introduction

 In current clinical practice, intermediate-risk prostate cancer (PCa) is typically managed using radical whole-gland treatment, such as robot-assisted radical prostatectomy (RP) or a form of radiotherapy (RT). These treatments are known to be associated with complications, mainly consisting of incontinence and erectile dysfunction, affecting 21% and 70% of patients with RP, respectively.^1^ For patients with RT, urinary complaints, such as frequency, urgency, urethral stricture or incontinence, are observed in up to 27% of the patients, erectile dysfunction in up to 29% and gastrointestinal toxicity in up to 11%.^2^ These side-effects from RT and RP can substantially impact quality of life (QoL) of patients.

PCa is a heterogenous disease, with a risk classification ranging from low to high risk, requiring different treatment approaches. While radical treatment for high-risk disease results in favourable oncological outcomes,^3^ evidence shows that active surveillance (AS) is a safe approach for low-risk PCa without increasing the risk of unfavourable outcomes.^4^ AS is close monitoring, using prostate-specific antigen (PSA), MRI and biopsies, of PCa without immediate treatment. Although intermediate-risk PCa often requires treatment, it is debatable if patients with less aggressive tumours than high-risk patients also require a radical whole-gland treatment.^5^

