### Interventions

The therapies within the intervention group are HIFU, TULSA and IRE. If a patient is assigned to focal therapy, the treatment a patient receives is based on the centre where the inclusion took place. This means that a patient is not able to choose what kind of focal therapy will be received in case of randomisation for focal therapy. The control group consists of RP or RT. If a patient is allocated to radical treatment, the patient will receive treatment as per current clinical practice in the Netherlands according to the Dutch guidelines. For RP, different types of approaches are possible, including nerve-sparing and non-nerve-sparing options, depending on tumour characteristics and anatomical considerations. Patients receiving RT will be treated as per national guidelines. Therapies administered can include RT with hypofractionation (28 fractions with 2.5 Gy, total dose of 70 Gy or 20 fractions with 3.1 Gy, total dose of 62 Gy) and RT with ultrahypofractionation (5 fractions with 7.25 Gy, total dose of 36.25 Gy). All RT regimens provide bio-equivalent doses similar to conventional RT consisting of 35 fractions with 2 Gy. According to the current national guidelines, the addition of androgen deprivation therapy (ADT) is not recommended for patients with intermediate-risk PCa with a PSA level of 20 ng/mL or lower. Patients eligible for both RP and RT are provided with evidence-based information, including a decision aid, to support shared decision making. The final treatment choice is made jointly by the patient and the urologist.

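### Clavien-Dindo, a surgical scale, is the only grading named for complications in both arms although part of the radical arm receives radiotherapy, so the planned complication risk differences may not compare like with like

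*Protocol article*

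**What the plan says.** The Analysis section of the protocol article fixes the scale: "Treatment-related complications will be recorded according to the Clavien-Dindo classification". It then sets out the comparison: "An overall risk difference for the overall complication rate and a 95% CI, and a risk difference per complication", the latter also with 95% CIs. The Interventions section says "The control group consists of RP or RT", with RT given in 5, 20 or 28 fractions. On collection, the Secondary endpoints section says "data will be collected on treatment-related complications occurring during or after the procedure", with no cut-off in time.

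The same section records other information on harm. Its list of endpoints includes "disease-specific mortality, all-cause mortality, adverse events, operating time, hospital care stay, pathology results", so adverse events appear by name, without a scale. On questionnaires it says "The EORTC QLQ PR-25 is a questionnaire to assess sexual problems and functioning, micturition, bowel symptoms and hormonal treatment side effects"; the ICIQ, IPSS and SHIM/IIEF-5 are added. They are completed at baseline and at "6 weeks, 3 months, 6 months, 12 months and annually thereafter for up to 60 months".

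The Introduction describes the harms of RT as urinary complaints in up to 27% of patients, then "erectile dysfunction in up to 29% and gastrointestinal toxicity in up to 11" per cent. For RP it gives incontinence in 21% and erectile dysfunction in 70%.

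**The concern.** Clavien-Dindo was built to grade departures from a normal postoperative course by the intervention needed to correct them. That suits RP and the focal procedures. It suits RT less well, because the harms listed for RT in the Introduction are largely symptoms whose importance lies in severity and duration, and many need no intervention. Under this scale such an event takes a low grade, or a site may not regard it as a complication at all.

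The plan recognises elsewhere that RT needs separate handling: where operating time is recorded for the other treatments, the type of radiation is registered for RT. It makes no matching arrangement for complications. Lower harm is a main argument for focal therapy, and the Discussion says the trial is meant to inform reimbursement and inclusion in standard care. A risk difference that pools events graded on a surgical scale with events the scale does not grade well would be hard to interpret in that setting.

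**Working it through.** **No figure to reproduce.** The article gives no expected complication rate, power or sample size for this endpoint. The check is therefore a reading of the text, followed by an illustration of scale.

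**Reading the text**

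1. *Scale.* One scale is named for treatment-related complications. There is no second scale and no exception for RT.
2. *Use.* The risk differences are for the overall rate and for each complication. Both measure occurrence, and no grade threshold is stated. Poor grading of an RT event distorts the description of severity. It changes the rate only if the event is not recorded.
3. *Recording.* Collection runs during or after the procedure. This neither excludes RT nor sets a time limit, but it also does not say how late or chronic RT effects are to be picked up.
4. *Other routes.* Adverse events are a listed endpoint, but the Analysis section describes no between-arm analysis of them other than the complication risk differences. The questionnaires cover urinary, bowel and sexual symptoms in both arms but do not feed those risk differences.

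**Illustration of scale, if only RT events were missed**

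Understatement of the radical-arm rate = RT share × RT toxicity rate × (1 − fraction recorded).

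Inputs:
- RT share: not stated; assumed 25% to 75%.
- RT toxicity rate: 11% (gastrointestinal) or 27% (urinary), from the Introduction. Both are upper figures. Each is taken alone, because their overlap is not given.
- Fraction recorded: not stated; assumed 50% to 75%.

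Results:
- Lowest: 0.25 × 11% × 0.25 = 0.7 points.
- Highest: 0.75 × 27% × 0.50 = 10.1 points.
- At an RT share of 50%: from 0.50 × 11% × 0.25 = 1.4 points to 0.50 × 27% × 0.50 = 6.8 points.
- With every event recorded: 0 points.

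**Against the precision of the comparison**

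95% CI half-width = 1.96 × √[p1(1 − p1)/n + p2(1 − p2)/n], with n = 356/2 = 178 per arm and assumed complication rates:
- 10% and 20%: 1.96 × √[(0.09 + 0.16)/178] = 7.3 points.
- 20% and 20%: 1.96 × √[(0.16 + 0.16)/178] = 8.3 points.
- 20% and 30%: 1.96 × √[(0.16 + 0.21)/178] = 8.9 points.

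The illustrated shift therefore runs from negligible to slightly more than one half-width.

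**Direction**

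The illustration lets only RT events go missing. Untreated functional symptoms after RP (21% and 70% in the Introduction) or after focal therapy could go unrecorded for the same reason, and the article gives no rates for focal therapy. The net effect on the difference between arms could go either way.

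**The case against.** A reader might infer that RT toxicity is under-captured in this trial and that the comparison is biased against focal therapy. The document does not support that. Grading is not capture: nothing tells sites to record only events that suit the scale, the risk differences count occurrence, and the collection wording has no end point. Nor is an effect specific to RT shown, because untreated functional harm after RP or focal therapy could be missed in the same way.

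A reader might also infer that Clavien-Dindo is the trial's only record of RT harm. It is not, given the separate adverse-event endpoint and the questionnaires to 60 months, whose items are analysed as the proportion of men with a moderate or big problem.

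Finally, a journal article may leave toxicity coding and time windows to the full protocol or the statistical analysis plan. That is fair for the window and for the adverse-event scale, and their absence is not the finding. It does not dispose of the point, because the article does name a scale for complications and plans a between-arm comparison of them. An analysis plan finalised before database lock also cannot easily change how sites recorded events years earlier.

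What remains is narrower: a stated choice of scale that does not fit one of the treatments being compared, with no account of how RT events enter the risk difference.

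**Conclusion.** The point holds for the complication comparison only. Clavien-Dindo is the sole scale named for treatment-related complications in both arms, and it does not grade RT toxicity by symptom severity. RT events may therefore be graded, and possibly recorded, on a different footing from RP and focal events. The size and direction of any bias cannot be determined from the document; the 0.7 to 10.1 points shown above rest on an assumed RT share, assumed incomplete recording and upper-limit toxicity rates used as expected values. Severity is minor: the endpoint is secondary, lies outside the definition of trial success in the Sample size section, and does not affect either co-primary conclusion.

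**What to change.** Grade all treatment-related adverse events in both arms prospectively on one modality-neutral scale (CTCAE), over a stated window common to both arms. Base the overall and per-complication risk differences on that scale, reported for any grade and for grade 3 or higher. Keep Clavien-Dindo as an added description of procedural complications after RP and focal therapy.

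The cost is one more grade field on the event form, a change of wording in the Analysis section, and double coding of procedural events. The Trial status section reports 110 of 356 patients enrolled in October 2025, so 246 were still to come and could be graded prospectively from the start. For those already enrolled, past events would need retrospective grading. That will be harder for RT patients, because the Design section has them referred to RT centres, where the notes may be held. Events graded retrospectively should be flagged so that a sensitivity analysis can set them aside.
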